### Frequencies of APOs

After applying the data harmonisation results, we found that approximately 34% of all pregnancies in the MOMI cohort were affected by adverse outcomes (**Table 2**). Pregnant women in Tanzania experienced the fewest number of APOs (18.33%), whereas pregnancies in women of the other two AMANHI sites (Bangladesh and Pakistan) resulted in the highest numbers of APOs (47.94% and 45.00%, respectively). SGA was the most common APO in the combined MOMI cohort (n = 3527, 21.74% of pregnancies), as well as at each site. PTB was observed in close to 10% of all pregnancies, ranging from 5.4% in Tanzania to 14.9% in Pakistan. PE and SB cases ranged from 0.23% to 3.30% and from 0.64% to 2.41%, respectively. The frequencies of the distinct APOs in the GARBH-INi cohort mirrored those observed in the MOMI cohort (**Table 2**).

**Table 2 T2:** Frequencies of adverse pregnancy outcomes

	GAPPS		AMANHI			Combined MOMI cohort	GARBH-INi
	**Zambia**	**Bangladesh**	**Bangladesh**	**Pakistan**	**Tanzania**		
**Number of Pregnancies**	2576	3644	3000	2500	4501	16 221	8100
**APO**	**Number of APOs (% of pregnancies)**						
**PTB**	223 (8.66)	384 (10.54)	366 (12.20)	372 (14.88)	242 (5.38)	1587 (9.78)	764 (9.43)
Very PTB (% PTB)*	45 (20.0)	14 (3.6)	40 (10.9)	20 (5.4)	29 (11.9)	148	72 (9.4)
**PE**	85 (3.30)	35 (0.96)	7 (0.23)	39 (1.56)	124^c^(2.75)	290 (1.79)	166 (2.05)
Early-onset PE (% PE)	35 (41.2)	7 (20.0)	3 (42.8)	9 (23.1)	22 (17.7)	76	13 (8.6)
Late-onset PE (% PE)	50 (58.8)	28 (80.0)	4 (57.2)	30 (76.9)	100 (80.6)	212	151 (91.0)
**SGA**							
SGA <10th percentile	434 (16.84)	936 (25.68)	1044 (34.80)	683 (27.32)	430 (9.55)	3527 (21.74)	2402 (29.65)
SGA <3rd percentile	167	385	525	304	170	1551	1167
**Stillbirth**	62 (2.41)	25 (0.69)	21 (0.70)	31 (1.24)	29 (0.64)	168 (1.04)	168 (2.07)
**Total number of APOs**	804 (31.21)	1380 (37.87)	1438 (47.94)	1125 (45.00)	825 (18.33)	5572 (34.35)	3500 (43.20)

AMANHI – Alliance for Maternal and Newborn Health Improvement, APO – adverse pregnancy outcome, GAPPS – Global Alliance to Prevent Prematurity and Stillbirth, MOMI – Multi-Omics for Mothers and Infants, PE – preeclampsia, PTB – preterm birth, SGA – small for gestational age

*Very PTB is defined as birth <31 weeks/6 days gestational age.

†Due to missing GA at birth, early-onset and late-onset PE cannot be derived for n = 2.

Thus, we have established a unique two-continent spanning cohort of pregnant women in LMICs, of which more than a third experienced APOs. Thousands of longitudinally collected specimens are now being analysed for genetic, proteomic, metabolomic, or nutrient factors associated with specific pregnancy outcomes. According to the study design (**Figure 3**), specimens from a single time point were selected for genomics analysis, whereas proteomic and metabolomic signatures will be determined using over 30 000 longitudinally collected maternal plasma samples (Table S1 in the **Online Supplementary Document**). Nutrients type I will be measured in >9500 maternal plasma and urine samples, and approximately 1200 maternal plasma samples for nutrients type II (Table S1 in the **Online Supplementary Document**). Specimen numbers for placental tissue analysis are listed in the relevant section below. To gain insights into potential biological factors that may impact infant morbidity and mortality and, considering the complex interactions of the mother-infant dyad, the same analytical tools are being applied to cord blood samples (Table S1 in the **Online Supplementary Document**).

## ANALYTICAL STUDIES

Genomics have emerged as a powerful tool to identify genetic risk factors, both maternal and foetal, of APOs [34-37]. As the association of genetic factors with certain outcomes generally requires a large sample size, the genomics analysis is performed for the full cohort to understand the genetic basis of pregnancy phenotypes and the variation of other omic features. The core steps include the generation of genomic data of maternal and foetal DNA samples using 1 × low-pass whole-genome sequencing, followed by high-quality imputations [38] using large reference panels [39]; conducting genomic analyses of multiple pregnancy phenotypes in mother/infant pairs collected from diverse populations; and integration with other omics measures. Given the close maternal-foetal interaction, pregnancy phenotypes are influenced by both genomes. Therefore, in addition to conventional genomic analysis in mothers and infants separately, the aforementioned genomic analysis will also be conducted in mother/child pairs using a haplotyped-based approach [25], in which a mother-child pair will be treated as the analytical unit with three haplotypes each with distinct maternal or foetal genetic effects. The haplotype-based genomic data analysis will be conducted at three different levels: genome-wide scan for single-variant associations; multi-variant analysis to examine the cumulative effects of multiple variants; and analysis of genome-wide variants to study the genetic architecture (Figure S4 in the **Online Supplementary Document**).

Epigenomics plays a vital role in understanding how genes interact with environmental factors during pregnancy, significantly influencing maternal and foetal health [40-42]. The MOMI study addresses two key questions in human pregnancy: the association between maternal epigenetic marks and pregnancy outcomes, and foetal epigenetic alterations resulting from suboptimal in utero exposures. The epigenomic analysis will be conducted on a selected subset of approximately 1500 pregnancies, enriched for cases of very PTB, PE, and SB (**Figure 3**). Genome-wide methylation profiling will be performed using the Infinium MethylationEPIC v2.0 BeadChip (Illumina Inc., San Diego, California, USA) on maternal DNA samples extracted from whole blood or buffy coats collected at enrolment, as well as foetal DNA extracted from cord blood or buffy coats (Figure S5 in the **Online Supplementary Document**). Future studies will analyse maternal blood samples collected during follow-up visits to investigate dynamic methylation changes throughout pregnancy. The proposed analytical aims include: testing maternal and foetal DNA methylation associations with pregnancy phenotypes and exposures; developing predictive models for APOs; interrogating methylation associations with maternal exposures, micronutrients, other omics measures; methylation quantitative trait loci (mQTL) analysis and causal inferences by Mendelian randomisation (MR). Although the current epigenomic subset presents power constraints, we will ensure the robustness of our causal inference by restricting analyses to cis-acting mQTLs with high instrumental strength (*e.g.* F-statistics >20) and accounting for ancestry heterogeneity using genetic principal components and stratified sensitivity analyses. With approximately 1500 samples, the study is adequately powered to detect cis-mQTLs explaining approximately 2–5% of methylation variance at stringent genome-wide significance thresholds (α ≈ 5 × 10^−8^). For phenotypic outcomes and MR analyses, this sample size allows for the detection of effects explaining approximately 0.6% of variance at a nominal significance level. To maximise discovery power, we supplement single-site MR with multi-variant approaches, including methylation risk scores and polygenic scores. These analyses are framed as supportive and hypothesis-generating, providing a methodological foundation for future consortium efforts that will expand epigenomic profiling to substantially larger samples.

Proteomics alone or in combination with other omics platform have been successfully applied to clinical phenotypes [43-46]. In the MOMI Consortium, the maternal plasma proteome will be defined across the whole pregnancy (Figure S6 in the **Online Supplementary Document**). The study is built upon perfloric acid workflow with neutralisation, an optimised, high-throughput plasma preparation workflow based on perchloric acid precipitation, which significantly reduces costs with great proteomic depth [47]. Samples are analysed using next-generation Thermo Orbitrap Astral (ThermoFisher Scientific, Rheinfelden, Germany) mass spectrometers, providing increased sensitivity and scanning speed essential for deep proteome analysis. To maximise statistical power for biomarker discovery, the study follows a ‘rectangular’ study design [48]. The proteomics analytical pipeline integrates both established and novel computational approaches, including the recently developed AlphaDIA software [49] and proceeds systematically starting from individual cohorts advancing to cross-cohort integration. Quality control measures include standardised reference samples and replicate analyses of pooled samples within each preparation batch. The computational pipeline employs dimensionality reduction and unsupervised clustering for sample classification, followed by statistical modelling to identify proteins associated with APOs, while accounting for confounding factors. Longitudinal analysis will map protein trajectories throughout normal pregnancy progression, providing critical context for identifying pathological deviations. Statistical approaches will be complemented by machine learning to identify predictive protein panels, facilitating the development of diagnostic and prognostic assays and prevention of APOs [50]. This multi-layered analytical strategy is designed to distinguish universal molecular signatures from population-specific variations, advancing our understanding of proteomics changes in pregnancy and their implications for maternal and foetal health.

The metabolome will be analysed by rapid liquid chromatography-mass spectrometry that performs nontargeted measurement of >11 000 small molecule biomarkers, ranging from very polar to very nonpolar molecules, and essentially captures their chemical properties. The analytical cycle time is estimated to be <1 minute per sample, amounting to a high-throughput capacity of >4000 specimens per day, enabling the full cohort metabolome analysis (Figure S7 in the **Online Supplementary Document**). There will be rigorous quality control from the rapid liquid chromatography-mass spectrometry function to data quality and sample integrity [51-53]. This pipeline allows identification of approximately 1000 known markers and measurement of >10 000 unknown/ novel molecules. Through comparative analysis and matching to existing metabolite libraries, the structure of compounds can be derived. Once the identity of the potential metabolic signatures linked to various pregnancy complications and adverse outcomes has been confirmed, validation will be conducted in the GARBH-INi cohort.

To understand the impact of nutrition in pregnancy on maternal, foetal, and newborn health, the Consortium aims to determine the prevalence of micronutrient deficiencies among pregnant women across different geographic sites; evaluate the associations of nutrients (single and combination of nutrients) with APOs; assess the temporal changes in maternal nutritional status during the course of pregnancy; assess the relationships between maternal and foetal (cord blood) nutritional status; evaluate interactions between maternal nutritional status, inflammation, and other omics; and understand the mechanisms by which micronutrients influence human pregnancy outcomes.

Due to the high cost-per-sample and medium/low sample throughput, a case-cohort study design categorised into the sub-cohort and nested case control study (**Figure 3**) was selected. The sub-cohort includes the longitudinal samples of approximately 30% of pregnant women in the full cohort and available cord blood samples for group I nutrient analysis (Figure S8 in the **Online Supplementary Document**). Nutrients of this group include vitamin A, D, E, folate, B12, total homocysteine, ferritin, transferrin receptor, iodine, minerals (copper, selenium, magnesium, calcium, phosphorus, iron, potassium, sodium), alpha-1-acid-glycoprotein, C-reactive protein, high-density lipoprotein, low-density lipoprotein, and triglycerides. It is noteworthy that the Group I Nutrient analyses will be performed by the icddr,b, representing the only in-country analysis. Group II nutrients (vitamins B1, B2, B3, B5, B6, B7, choline, and a targeted metabolomics panel) will be analysed in the longitudinal samples of PE, SB, and vPTB cases and their matched term controls (1:3 ratio). The B vitamins, choline and related metabolites will be measured by ultra-high performance liquid chromatography (UHPLC)- MS/MS and fatty acids and amino acids by UHPLC-MS/MS – MxP®Quant 500 XL kit [51,54].

As specimens of the GARBH-INi cohort will be analysed by the Translational Health Science and Technology Institute, India (THSTI), a harmonisation plan between THSTI and icddr,b, or between THSTI and UC Davis for nutrient group I or group II analyses, respectively, was developed. Institutions will apply standardised test methods, instrument calibration, quality control measures, external quality assurance schemes, and reporting methods. The joint analysis of the nutrient group I and II parameters from the GAPPS, AMANHI and GARBH-INi sites will allow for validation across sites and analytical platforms.

The placenta tissue analysis will be particularly valuable towards the goal of designing novel diagnostics or intervention strategies to prevent APOs, as several of the APOs are either entirely or partially attributable to placental dysfunction. These include early-onset PE, foetal growth restriction, and a subset of PTB cases. Since the placenta is in direct contact with maternal blood, placental APO signatures will likely be highly complementary to APO signatures in maternal blood and provide crucial information on the involvement of certain biological pathways.

The placental tissue analysis will be limited to a smaller sample subset (as working with this tissue is labour intensive and impossible to scale-up) and focused on PTB as a common APO at all sites. Placental tissues will be profiled in a 1:2 case-cohort study by histopathology (154 PTB *vs.* 323 TB), bulk transcriptomics (26 PTB *vs.* 56 TB), single nuclei RNA and ATAC sequencing (15 PTB *vs.* 30 TB) and global proteomics by laser capture/ MS (32 PTB *vs.* 62 TB). Only one biopsy was available for the morphological analyses. Due to regional variations in placental microanatomy and based on preliminary data from the pilot study, a single endpoint (inflammation) is being evaluated [23,55]. The endpoints of the other technologies are identification of differentially expressed placental genes and proteins in placenta tissue of women with PTB *vs.* TB. The candidate biomarkers will be verified by comparisons with public databases and equivalent data from the GARBH-INi cohort.

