For non-machine learning association analyses, we will use a prespecified covariate framework grounded in clinical relevance and established epidemiologic confounders, including maternal age, body mass index, parity, GA at sampling, and study site. These variables will be incorporated within mixed-effects or hierarchical regression models to appropriately account for cohort structure and site-level heterogeneity, with model specifications defined *a prior* to avoid data-driven overfitting. To control for false-positive findings across the large number of molecular features tested, we will apply false discovery rate correction within each omics layer and, where appropriate, across integrated analyses.

Although statistical harmonisation approaches such as ComBat are effective at reducing batch effects, they may inadvertently remove meaningful biological or population-level differences between sites. Therefore, our primary framework prioritises external validation across sites as the most conservative test of reproducibility and transportability. Rather than relying solely on post hoc harmonisation, our primary strategy is to evaluate robustness and generalisability directly. Specifically, we will train models on subsets of study sites and validate them on held-out sites. This design allows us to assess real-world performance under true site-level variation, including differences in GA assessment, biospecimen handling, and sociodemographic context. This cross-site training and validation framework ensures that identified signatures are not artifacts of a single cohort, platform, or operational pipeline, but instead reflect patterns that are stable across diverse populations. Only models and associations that replicate across sites will be interpreted as biologically meaningful, providing a principled basis for pooled analyses. As a complementary, secondary analysis, we will apply ComBat-based correction and mixed-effects modelling to quantify and compare the impact of site-level harmonisation. This layered approach allows us to rigorously test whether pooled analyses are justified, distinguish technical from biological sources of heterogeneity, and preserve interpretability, while maintaining statistical rigor across structurally heterogeneous cohorts.

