Our planned MR analyses will be guided by a biologically motivated causal framework in which genetic variation precedes molecular variation, which in turn influences pregnancy outcomes. This framework is well supported by prior literature demonstrating causal relationships between genetically regulated trait, such as height, BP, glucose metabolism, lipid levels, and inflammatory processes, and pregnancy outcomes. Where MR is applied, instruments will be selected using established criteria, such as strong association with the exposure (genome-wide significance), independence from confounders, and absence of horizontal pleiotropy (assessed via sensitivity analyses such as MR-Egger and leave-one-out tests). Genetic instruments for molecular traits will be restricted to cis-acting variants where possible to enhance biological interpretability. Together, the MOMI study cohort design and analytical approaches ensure statistical efficiency, cost-effectiveness, and unbiased inference, while enabling robust discovery and validation of molecular signatures across rare and common pregnancy outcomes.

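### Two epigenomic power figures are not met as stated: a 2% cis-mQTL has about 52% power, and the 0.6% figure fits direct association but not Mendelian randomisation

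*Protocol article*

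**What the plan says.** The relevant text is the epigenomics paragraph of Analytical studies in the protocol article. It sets the sample: "The epigenomic analysis will be conducted on a selected subset of approximately 1500 pregnancies, enriched for cases of very PTB, PE, and SB". It then makes two power statements.

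- For mQTLs: "With approximately 1500 samples, the study is adequately powered to detect cis-mQTLs explaining approximately 2–5% of methylation variance at stringent genome-wide significance thresholds", with alpha given as about 5 × 10⁻⁸.
- For phenotypic outcomes and MR analyses jointly: "this sample size allows for the detection of effects explaining approximately 0.6% of variance at a nominal significance level".

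No target power and no sidedness are given. For MR, the paragraph restricts instruments to cis-acting mQTLs with an F-statistic above 20, as an example of adequate strength. It also concedes power constraints in this subset, adds methylation risk scores and polygenic scores to single-site MR, and labels the analyses as supportive and hypothesis-generating.

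**The concern.** Both statements can be checked from the article's own inputs. The lower end of the mQTL range looked too optimistic for so strict a threshold. Giving one figure to direct association and to MR looked wrong in principle. An MR test sees the exposure only through its genetic instrument, so the signal in the outcome shrinks by the share of exposure variance that the instrument explains.

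The stake is interpretation. Moving beyond association to mechanism is a declared goal in Data analysis and data integration, and MR is one of the tools set out for it. A reader who takes 0.6% as the size of causal effect that MR can detect at n = 1500 would overrate what a null MR result shows.

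**Working it through.** **Inputs.** From the epigenomics paragraph: n ≈ 1500; mQTL effect R² = 2–5%; alpha = 5 × 10⁻⁸; detectable effect for phenotype and MR R² = 0.6%; instrument F > 20. Assumed because not stated: two-sided tests, nominal alpha = 0.05, and 80% as the usual reading of adequate power.

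**Method.** One-degree-of-freedom linear association test, noncentral F with 1 and 1498 df, noncentrality λ = nR²/(1 − R²).

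**1. The plan's 0.6% for direct association.** λ = 1500 × 0.006/0.994 = 9.05. Power at two-sided 0.05 is 85%; 80% power is reached at 0.52% and 90% at 0.70%. The figure reproduces for a single direct test in all 1500.

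**2. The mQTL range at 5 × 10⁻⁸.**

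| R² | λ | Power |
|---|---|---|
| 2.0% | 30.6 | 52% |
| 2.5% | 38.5 | 76% |
| 2.6% | 40.0 | 80% |
| 3.0% | 46.4 | 91% |
| 5.0% | 78.9 | >99.9% |

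At 2%, the normal and Fisher-z approximations and an adjustment for 20 covariates give 51% to 53%; a one-sided alpha gives 57%. For 80% power at 2%, n would have to be about 1950.

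**3. MR with a single instrument.** The variance in the instrument–outcome test is

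R²(instrument–outcome) = R²(instrument–exposure) × R²(exposure–outcome).

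For 80% power at two-sided 0.05, the exposure must therefore explain at least

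(1.960 + 0.842)² / (n × instrument R²) = 7.85/1500 ÷ instrument R² = 0.52% ÷ instrument R².

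Power at an exposure effect of 0.6% follows from the normal approximation with mean √(1500 × instrument R² × 0.006).

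| Instrument R² | Exposure–outcome R² for 80% power | Multiple of 0.6% | Power at 0.6% |
|---|---|---|---|
| 2% | 26% | 44 | 7% |
| 5% | 10% | 17 | 10% |
| 30% (illustrative) | 1.7% | 2.9 | 38% |

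Simulation with 3000 runs per setting gave 7.2% and 9.9% power for the first two rows. An instrument just meeting F = 20 has R² = 20/(20 + 1498) = 1.3% and would need an exposure explaining about 40%.

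Turned round, MR reaches 80% power for a 0.6% effect at n = 1500 only if the instrument explains 0.52/0.6, or about 87%, of the exposure variance.

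**The case against.** The strongest reply is that little is wrong and that the text already hedges. The range is given as approximate, no target power is named, and the 80% threshold of 2.6% lies inside it, so the lower bound is off by about 1.3-fold (2.6/2). The 0.6% is correct for phenotypic outcomes. The paragraph concedes power constraints and calls the work hypothesis-generating. All of that stands and limits the severity. It does not make 52% adequate, and it does not turn 0.6% into an MR effect size.

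A reader might infer that MR here is underpowered 17- to 44-fold, or has almost no power. The documents do not support that as a general result. The 2–5% is an mQTL size said to be detectable, not the strength of the instruments to be used. F > 20 is a floor that stronger cis-mQTLs also pass, and multi-variant scores are planned as well. The shortfall depends on instrument R², which is not given.

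The outcome associations might also use the full genotyped cohort. With 16 221 women, the minimum falls to 2.4% for a 2% instrument and 1.0% for a 5% instrument, and an instrument of about 8.1% (7.85/(16 221 × 0.006)) would reach 0.6%. But the sentence ties its claim to the sample of about 1500. Equally, if 0.6% means the instrument–outcome association, the arithmetic holds, but that is not the causal effect and the text does not say so.

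Three further inferences also lack support:

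- That the nominal level conflicts with the later statement "we will apply false discovery rate correction within each omics layer". The power sentence openly says nominal and does not claim to describe a corrected scan.
- That F > 20 contradicts the genome-wide significance criterion in the MR paragraph of Data analysis and data integration. The former is an example and a minimum, and an instrument meeting the stricter rule meets both.
- That per-outcome power at a Bonferroni level can be computed. Neither the number of methylation sites tested nor separate control sets within this subset are given.

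**Conclusion.** The point holds in two limited parts. First, adequate power for cis-mQTLs starts at about 2.6% of methylation variance, not 2%, where power is about 52%; the rest of the range to 5% is sound. Second, 0.6% is a direct-association figure wrongly extended to MR. At n = 1500 the MR detectable effect is 0.52% divided by the instrument R², which exceeds 0.6% for any instrument explaining less than about 87% of the exposure.

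The conclusions assume two-sided tests, nominal alpha of 0.05, an 80% target, a linear model with all 1500 analysed, and exposure and outcome both measured in that subset. The mQTL result is stable across the approximations tried. The size of the MR gap depends on instrument strength. Severity is modest: the analyses are declared hypothesis-generating, and nothing in the epigenomics paragraph shows the subset size being derived from these figures.

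**What to change.** Reword the two sentences in the epigenomics paragraph.

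- mQTLs: state that about 1500 samples give 80% power for cis-mQTLs explaining about 2.6% or more of methylation variance at 5 × 10⁻⁸ (about 52% at 2%, 91% at 3%), and name the target power and sidedness.
- Direct association: confine the 0.6% to a single direct test in all 1500 at two-sided 0.05, with 85% power.
- MR: add a separate sentence or small table giving the detectable exposure effect as 0.52% divided by the instrument R², with the instrument strengths the team expects. If outcome data will come from a larger set than the 1500, say so and use that n.

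The cost is wording only, with no new samples, assays or analyses. The stated sensitivity becomes less favourable, mainly for MR with weak instruments.

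### At about 1500 samples and α of 5 × 10⁻⁸, power at the 2% end of the stated cis-mQTL range is about 52%; 80% power starts at about 2.6% of methylation variance

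*Protocol article*

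**What the plan says.** The epigenomics paragraph of the protocol article (Analytical studies) sets the sample size: "The epigenomic analysis will be conducted on a selected subset of approximately 1500 pregnancies". It then claims that, with about that many samples, "the study is adequately powered to detect cis-mQTLs explaining approximately 2–5% of methylation variance at stringent genome-wide significance thresholds", and puts α at about 5 × 10⁻⁸. It gives no numeric power, sidedness or formula.

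The next sentence makes a second claim, for phenotypic outcomes and Mendelian randomisation (MR): "this sample size allows for the detection of effects explaining approximately 0.6% of variance at a nominal significance level".

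The same paragraph admits that the subset is constrained in power, restricts causal inference to cis-acting mQTLs of high instrumental strength (an F-statistic above 20 is the example), and presents the analyses as supportive and hypothesis-generating. The Data analysis and data integration section lists genome-wide significance among the criteria for choosing MR instruments.

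**The concern.** A variant that explains 2% of variance in 1500 samples has an expected test statistic very close to the critical value at 5 × 10⁻⁸. Such a variant is detected about half the time, which is not what a reader understands by adequate power.

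Two things are at stake:

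- **Instrument yield.** Genome-wide significance is one of the article's instrument criteria, so power at that threshold bears on which methylation sites can enter MR. For variants near 2%, the yield would be lower than the sentence suggests.
- **Reading of null results.** Someone relying on the stated range would take failure to find a 2% cis-mQTL as better evidence of absence than it is.

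**Working it through.** **Inputs, all from the epigenomics paragraph**

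- n = 1500 (stated as approximate).
- R² from 2% to 5%.
- α = 5 × 10⁻⁸. Sidedness is not stated; a two-sided, one-degree-of-freedom test is assumed, and one-sided is tried below.
- Target power: not stated; 80% is assumed as the conventional floor.

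**Formula.** For a regression on one variant, the test statistic follows a noncentral F(1, n − 2) distribution with noncentrality λ = n·R²/(1 − R²). Power is the probability of exceeding the central F critical value at α. With 1498 denominator degrees of freedom that critical value is 30.0.

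**The plan's claim.** At R² = 2%, λ = 1500 × 0.02/0.98 = 30.6, against the critical value of 30.0. Adequate power at the lower end is not reproduced.

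| R² | λ | Power |
|---|---|---|
| 2.0% | 30.6 | 52% |
| 2.5% | 38.5 | 76% |
| 2.6% | 40.0 | 80% |
| 3.0% | 46.4 | 91% |
| 5.0% | 78.9 | >99.9% |

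Solving for R² gives 2.6% for 80% power and 3.0% for 90%. Holding R² at 2% would need n of about 1955 for 80% power or about 2236 for 90%.

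**Does another reasonable reading rescue 2%?**

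- Noncentral chi-square with λ = n·R²/(1 − R²): 53%. With λ = n·R²: 51%. Fisher z: 52%.
- Twenty covariate degrees of freedom removed: 52%.
- One-sided α: 57%.
- n read generously as 1600: 59%; as 1700: 66%.

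None comes near 80%. Across the two-sided methods, the smallest R² with 80% power is 2.57% to 2.64%; one-sided it is 2.5%.

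**The adjacent claim as a benchmark.** At R² = 0.6%, λ = 1500 × 0.006/0.994 = 9.05. If the nominal level means two-sided 0.05, the critical F is 3.85 and power is 85%. Requiring the same 85% at 5 × 10⁻⁸ gives R² of about 2.8%. The two neighbouring power statements therefore do not share one standard, and the cis-mQTL lower end is the one that falls short.

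**The case against.** **The benchmark is not the article's.** It says only that "the study is adequately powered to detect" this range, prefixed by an approximation. That is true, and 80% is an assumption. But about 52% is not adequate by any usual convention, and the neighbouring 0.6% figure implies about 85%.

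**The article already limits reliance on the figure.** It concedes power constraints, adds multi-variant scores, calls the work hypothesis-generating and defers to larger future samples. This stands as a limit on the consequence. It does not correct the number: the caveats are general, and nothing qualifies the 2% end.

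**The error touches little of the range.** Also true. The interval from 2.0% to 2.6% is one fifth of the stated span (0.6 of 3.0 percentage points).

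Three stronger inferences are tempting and go too far.

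- *About half of all instruments would be lost.* That proportion applies only to variants at about 2%, and the loss falls quickly above it. Under the F > 20 example alone, a 2% variant would pass about 85% of the time. The genome-wide criterion stated later is stricter (F of about 30), so this softens the argument about instrument yield without removing it.
- *Selection would seriously inflate the MR estimates.* A truncated-normal approximation gives an average inflation of about 14% for significant variants at 2%, 5% at 2.6% and 3% at 3%. It matters only if instruments are selected and estimated in the same sample, which the article does not settle.
- *The ancestry-stratified analyses are hopelessly underpowered.* The article mentions "accounting for ancestry heterogeneity using genetic principal components and stratified sensitivity analyses" but attaches 5 × 10⁻⁸ only to the full sample. It neither says that strata are tested at that level nor gives their sizes. If strata merely rechecked variants already found, at 0.05 and with 300 women (both assumptions), power would be about 98% at 5% of variance and 69% at 2%. No conclusion about the stratified analyses follows from the document.

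**Conclusion.** The concern holds for the lower end of the range only. At n = 1500 and two-sided α of 5 × 10⁻⁸, the adequately powered range is about 2.6% to 5% of methylation variance, not 2% to 5%. The 52% figure rests on the article's own n, R² and α and on a standard single-variant regression test. The 2.6% figure also rests on the assumed 80% target; it becomes about 2.8% at the 85% implied by the adjacent claim and about 3.0% at 90%.

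The weight is modest. This is a verifiable misstatement in a supportive analysis. It bears on the expected yield of MR instruments and on how a null result near 2% is read, and it does not call the study design into question.

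**What to change.** Name the target power and sidedness, and restate the sentence, for example: *with approximately 1500 samples there is at least 80% power (two-sided α of 5 × 10⁻⁸) for cis-mQTLs that explain about 2.6% or more of methylation variance; power at 2% is about 52%*. If the authors prefer 90% as the target, the lower bound becomes about 3.0%. Stating the α and power behind the 0.6% figure in the same place would put both claims on one standard.

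The cost is one sentence and one slightly less favourable figure. No change to sample size, assays or analysis is needed, and no added statement about the stratified analyses is called for.
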